### Trial design {8}

The present study is planned as a randomized controlled treatment trial, involving a guideline-based psychiatric treatment (general psychiatric management (GPM) [20]) for BPD, over the course of a program comprising 4 months of treatment plus 12 months of follow up, in comparison with 4 months of TAU, by focusing on the underlying mechanisms of change. The outcome part is a superiority trial, while the mechanisms part focuses on controlled comparison of processes of change.

## Methods: participants, interventions, outcomes

### Study setting {9}

The trial takes place in the context of Lausanne University Hospital and the University of Lausanne, Switzerland.

### Ethical clearance

With respect to the submitted project on the Swiss Ethics platform, the competent Canton de Vaud Ethics Committee, has approved the study (2017–02167). The study is registered (NCT0317818). In keeping with the established and approved data management plan, only anonymous data will be kept in the file. All raw video data, where the patient may be identified, and fMRI data will be stored separately from patient identifiers and from the main dataset.

### Eligibility criteria {10}

Patients with BPD according to the *Diagnostic and statistical manual of mental disorders, fifth edition* [72] and who have sufficient mastery of French will be included. The rate of comorbidity is expected to be high. All patients who accept participation in the study by giving informed written consent will be included in the outcome and mechanisms parts of the study; a sub-group of patients who fulfil additional inclusion criteria (female, younger than 45 years, right-handed, on stable medication or no medication and absence of formal counter-indication on the security check) will be included in the fMRI part of the study.

Patients with neurocognitive disorder, psychosis and bipolar disorder I will be excluded from the trial. In order to ensure generalizability of the results to a wide variety of clinical settings, no other exclusion criteria will be applied.

### Who will take informed consent? {26a}

After the patient makes a request for treatment at the Department of Psychiatry, University of Lausanne, for problems related to BPD, the patient meets with a researcher who explains to him/her the study and informs him/her about the randomization and the assessment schedule. On the consent form, participants will be asked if they agree that their data be used should they choose to withdraw from the trial. Participants will also be asked for permission for the research team to share relevant data with people from the Universities taking part in the research or from regulatory authorities.

### Additional consent provisions for collection and use of participant data and biological specimen {26b}

This trial does not involve collecting biological specimens for storage {26b; 33}. The relevant consent form can be obtained from the corresponding author upon request {32}.

## Interventions

### Explanation for the choice of comparators {6b}

In order to test the hypotheses, a brief version of Good Psychiatric Management (GPM) is compared with a brief version of treatment of usual. This is in keeping with standard methodological recommendations in the study of effectiveness of psychotherapeutic interventions.

### Intervention description {11a}

Brief treatment encompasses the communication about diagnoses, problem areas, anamnesis, the work on treatment focus, objectives and motivation, the treatment of treatment-interfering problems and the elaboration of interpretations related to the core concept of interpersonal hypersensitivity, according to the principles of GPM for BPD [20, 73–75]. For the TAU, 10 therapists will intervene using non-specific crisis management as usual (minimal ethical assessment and contact with the patient according to the local directives, ensuring safety management).

### Criteria for discontinuing or modifying allocated interventions {11b}

Should a participant request discontinuation of the intervention, the study therapist will use this as criteria for discontinuing and modifying the allocated intervention.

### Strategies to improve adherence to interventions {11c}

Therapist adherence to the protocol will be self-assessed by the therapist using Gunderson’s (2016) questionnaire for adherence to GPM principles, to be filled in after each treatment.

### Relevant concomitant care permitted or prohibited during the trial {11d}

Relevant concomitant care was permitted during the trial, and was recorded.

### Provisions for post-trial care {30}

The data management plan (see below) outlines procedures in the case of adverse events in the context of the trial, which includes provision, if needed of post-trial care in the case of harm.

### Outcomes {12}

The main outcome measure is the Zanarini Rating Scale for Borderline Personality Disorder (ZAN-BPD) [76]. The ZAN-BPD is a continuous hetero-administered measure assessing the nine criteria outlined in DSM-5, on a continuous Likert-type scale ranging from 0 to 4. As such, it yields a total theoretical score of 36. A comprehensive validation study has shown its reliability, validity and sensitivity to change [76].

Emotion processing related to self-criticism will be assessed using the self-criticism task. This task involves two main steps: (1) conduct of a two-chair dialogue on self-criticism, an individualized and therefore particularly emotion-arousing procedure [35, 54, 77] and observer’s process rating of the patient’s emotions using the Classification of Affective Meaning States (CAMS) [78] (see also [34, 47]) with the aim of extracting 20 individualized self-critical words for each patient at each assessment point. Increase in emotion flexibility (i.e., more different emotion categories as a reaction to the self-criticism) over time, along with a decrease in self-contemptuousness associated with the self-criticism over time, are indicators of productive change; (2) 1 week later, a test of neural correlates of the processing related to the 20 individualized self-critical words (extracted from step 1), in comparison with a set of 20 negative emotional [79], 20 positive emotional [79]), 20 neutral words and 20 non-words (symbols; in total 100 words; presented in a random order). Self-reported emotional arousal (on a self-assessment manikin (SAM)) and self-esteem (on the State Self-Esteem Scale (SSES)), along with observer-reported fear/shame (on the CAMS) reaction, will be measured as manipulation checks for step 1; SAM assessment will be performed for each stimulus presented in the scanner. This task was empirically tested in a non-published pilot study: in 5 individuals, we showed higher subjective arousal levels for the individualized words than for the standardized negative words, along with comparable neurofunctional activations.

Change in socio-cognitive processing of interpersonal patterns will be assessed using two independent tasks, one behavioral, and the other fMRI. The behavioral task involves the conduct of a structured interview using the Relationship Anecdote Paradigm [66] and based on this video-taped structured material, the observer’s process rating of the patient narrative using the CCRT [66–68] with the aim of comparing its pervasiveness pre-follow-up to post-follow-up (see Fig. 1). Decrease in CCRT pervasiveness is an indicator of productive change. The fMRI task involves the appreciation of humoristic stimuli measuring the patient’s theory of mind; this task has previously been validated for BPD [69] (for the validation of the stimuli see [80, 81]). It involves the processing and understanding of three sets of stimuli, presented in a pseudo-random order: (1) theory of mind (ToM): visual jokes requiring attribution of false mental states to the protagonists presented in the cartoons (30 stimuli); (2) visual puns (PUN): visual puns, i.e., cartoons that are based on visual similarities, not requiring attribution of false mental states (30 stimuli) and (3) a non-humorous control condition with incongruent visual information (30 stimuli, in total *N* = 90). Manipulation checks involve the assessment of the understanding of each joke. Decrease in activation of the ToM network over time is an indicator of productive change.

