### Emotion processing: change in affect-meaning states related to self-criticism

Change in emotion processing is central for psychotherapy in patients with BPD [37]. Greenberg and colleague (2006) have differentiated between, among others, emotion regulation and emotion transformation [38]. With regard to emotion regulation over the course of psychotherapy, Neacsiu and colleagues (2010) showed that the acquisition of specific coping-skills strategies, aiming at more efficient emotion regulation, functioned as a mediator of change in DBT [39]. These findings are in line with the results of a pilot functional magnetic resonance imaging (fMRI) study: Schnell and Herpetz (2007) investigated cognitive reappraisal over the course of inpatient DBT in six patients with BPD [31]. The authors identified a decrease in activation over the course of therapy at the levels of the right anterior cingulate cortex (ACC), the temporal and posterior cingulated cortex and the left insula [31]. Using a previously validated procedure of cognitive reappraisal [40], Schmitt and colleagues (2016) partially confirmed these results in a sample of patients with BPD (*N* = 32 patients) undergoing DBT and identified enhanced neural connectivity between ventro-lateral pre-frontal cortex areas and the amygdala [32], consistent with the neuropathological model put forward by New and colleagues (2007) [41]. Comparable results were obtained in 11 patients with BPD undergoing DBT, compared with 11 healthy controls: decreased amygdalar reactivity was identified after DBT [42, 43]. Consistent results were identified for change in distraction as a strategy for regulation of emotion [44] and change in pain-mediated regulation of emotion [45]. Perez and colleagues (2015) identified consistent effects in favor of enhanced fronto-limbic connectivity after 1-year long transference-focused psychotherapy (TFP) in 10 patients with BPD [46]. Taken together, these results suggest improved emotion regulation capacities after therapy in patients with BPD, but more research integrated within a larger theoretical framework is needed.

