Emotion transformation related to self-criticism is underpinned by biological changes. Using standardized stimuli, Longe et al. (2010) showed in a female student sample (*N* = 17) a blood oxygen level dependent (BOLD) activation (intra-subject comparison to a neutral condition at the level *p* < .05 corrected) in the left pre-frontal cortex (PFC; Brodman area (BA) 45), in the lateral orbito-frontal cortex (OFC; BA 47), in the left dorsolateral PFC (BA 9) and in the inferior and middle temporal gyrus (BA 20 and 21, including the lingual gyrus, BA 19) [55]. The hyperactivity in pre-orbito-frontal and orbito-frontal regions associated with self-criticism in this study was interpreted as linked with the inhibitory behavior known to be associated with activation of the lateral PFC [56]. Brain activity in the striatum has been associated with self-punishing emotions of self-criticism [54], such as shame, anger about the self and self-contemptuousness [35]. In addition, some regions of the insula-basal ganglia networks are known to be associated with processing of disgust [57]. In an fMRI study using *individualized* self-critical stimuli (which were previously selected based on a large set of words), Doerig and colleagues (2013) showed bilateral insula activation, along with activations in left hippocampus and amygdalar formations, interpreted as regions recruited in emotion processing of self-critical stimuli [58]. More research is needed to understand change in self-contemptuousness and its neuronal substrates over the course of treatment for BPD, when an individualized measurement method is applied.

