### Objectives {7}

(1) Outcome: a 10-session BPD-specific guideline-based treatment produces more reduction in specific borderline symptoms than non-specific treatment as usual (TAU). (2) Global change: a 10-session BPD-specific treatment presents pre-post change in socio-cognitive processing (SCP) and emotion processing (EP), which is not the case in the TAU. (3) Treatment response: SCP and EP change more in treatment responders, compared to non-responders (across conditions). (4) Mediation: the changes in these potential mechanisms of change will function as mediators of symptom decrease (between intake, discharge and follow up; the latter will be used to disentangle potential time confounds). Change is operationalized on behavioral and neurofunctional (by controlling for the corresponding behavioral/idiographic information) levels. For post-therapy EP, we expect greater emotional variability when dealing with individualized self-criticism, along with lesser self-contemptuousness, compared with pre-therapy. It is expected that post-therapy neuronal activations are lower in a EP network involving areas in the PFC, the striatum and the insula-basal ganglia [57, 58], when compared with pre-therapy. For post-therapy SCP, we expect lower CCRT pervasiveness, when compared with pre-therapy and we expect that post-therapy neurofunctional activations are lower in regions associated with the theory of mind (i.e., anterior cingulate, precuneus, inferior and middle frontal gyri and inferior parietal lobes) [69–71], compared with pre-therapy.

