For the fMRI assessments, we will use the methodology of blood-oxygen-level-dependent (BOLD) imaging followed by standard data processing and statistical analysis in the framework of Statistical Parametric Mapping software (SPM12). The fMRI data will be acquired on a Siemens Prisma 3 T (64-channel head coil using a 2D echo planar (EPI) sequence). The acquisition parameters will be as follows: 3 × 3 × 3 mm3: echo time (TE) =30 ms, slice repetition time (TR) = 66 ms, 30 slices, flip angle = 90°. The structural MRI data consist of T1-weighted MPRAGE images (TR = 2000 ms; inversion time (TI) = 920 ms; α = 9°; bandwidth (BW) = 250 Hz/pixel; readout in inferior-superior direction; field of view (FoV) = 256 × 232 mm; 176 slices) at 1 mm resolution. All data pre-processing will be performed using the SPM12 (Wellcome Trust Centre for Neuroimaging, shttp://www.fil.ion.ucl.ac.uk/spm/) running under Matlab 7.13 (The MathWorks, Inc., Natick, MA, USA). EPI images will be realigned to the subject’s average image across trials (corrected for spatial distortions using the SPM fieldmap tools). The parameters of registration to standardized Montreal Neurological Institute (MNI)-defined space will be calculated on the anatomical image and the default settings of the “unified segmentation” framework followed by the diffeomorphic registration algorithm DARTEL [106, 107]. The spatial registration parameters will be applied to the functional time-series co-registered to the corresponding individual’s anatomical scan. Prior to statistical analysis, we will apply spatial smoothing with a Gaussian kernel of 8 mm full-width-at-half-maximum. All statistical analyses will be performed using the default settings in SPM12. The statistical analysis at subject-specific level will be performed using the general linear model (GLM) after convolving the event onsets with a canonical hemodynamic response function [108]. Both time points will be modeled as two separate sessions within the design matrices. For the EP task, at the subject level we will calculate the interaction between words (self-critical versus standard negative words; the non-words and the negative words will be excluded from the analyses, but used as control variables to ensure cognitive appropriateness) and time (time point 1 versus time point 2) using symbols as baseline. For the SCP task, the subject-level differential *t* contrast will test the interaction between ToM, PUN and time point (the control stimuli will be excluded from the data analysis, but will serve as control for cognitive appropriateness). For both tasks, we will use the one-sample *t* test with the outcomes and arousal changes associated with treatment as regressors for the group-level analyses. The differential contrasts at the group level will test for positive and negative correlation between the interaction at the subject-specific level and BOLD signal changes. Where appropriate, we will control for the corresponding behavioral data from the same assessment point.

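### The only emotion-processing fMRI contrast named tests specificity against other negative words, not the predicted fall in activation, and the neutral words that could test that fall enter no named contrast

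*Protocol article*

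**What the plan says.** All references are to the protocol article.

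- **Prediction.** Objectives {7} expects that "post-therapy neuronal activations are lower in a EP network involving areas in the PFC, the striatum and the insula-basal ganglia" compared with before therapy. The sentence before it concerns individualized self-criticism, but the activation prediction is not stated relative to other negative words.
- **Stimuli.** Outcomes {12} describes five sets of 20 in the scanner task: individualized self-critical, negative, positive and neutral words, and non-words, which are the symbols.
- **Contrast.** The fMRI paragraph of Statistical methods {20a} says of the emotion-processing task that at subject level "we will calculate the interaction between words (self-critical versus standard negative words" and time, using symbols as baseline. The same sentence then removes the non-words and the negative words from the analyses and keeps them only as control variables. Neutral words are not mentioned.
- **Pilot.** Outcomes {12} reports, from an unpublished pilot of five people, "higher subjective arousal levels for the individualized words than for the standardized negative words, along with comparable neurofunctional activations".
- **Composite.** Statistical methods {20a} combines change in contemptuousness with change in regions of interest for individualized self-criticism. It does not say which contrast supplies the regional change.

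**The concern.** The prediction is about a fall, whereas the contrast is about a difference between two falls. If treatment lowers the response to self-critical words and to negative words alike, the prediction is true and the contrast is null. That result could be reported as no neural change in emotion processing.

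A comparison closer to the prediction is already in the design. The frontal activations that the background section reports for self-criticism came from an "intra-subject comparison to a neutral condition", and this trial shows neutral words in the scanner. No contrast in the plan uses them.

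**Working it through.** **Step 1: what the contrast estimates.** Let S, N, U and B be the responses to self-critical words, standard negative words, neutral words and symbols, with 1 and 2 for the two time points. The planned contrast is

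[(S2 − B2) − (N2 − B2)] − [(S1 − B1) − (N1 − B1)] = (S2 − S1) − (N2 − N1).

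The symbols drop out at each time point. What is left is the change for self-critical words minus the change for negative words.

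**Step 2: how much of a fall survives.** If S falls by δ and N falls by kδ, the contrast equals −(1 − k)δ. Self-critical versus neutral words by time gives (S2 − S1) − (U2 − U1), which is −δ if the neutral response does not change. With assumed values S1 = N1 = 1 and δ = 0.4:

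| Share k of the fall also seen for negative words | Self-critical vs negative, by time | Self-critical vs neutral, by time (neutral unchanged) |
|---|---|---|
| 0 | −0.4 | −0.4 |
| 0.5 | −0.2 | −0.4 |
| 1 | 0.0 | −0.4 |

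A fall confined to self-critical words is kept in full. If the two word types do start equal, a negative interaction requires self-critical words to activate less than negative words after therapy. Objectives {7} does not say that.

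**Step 3: illustrative power.** The plan gives no size for the scanned sub-sample, no within-person fMRI effect and no k, so all three are assumed. The test is a one-sample t test, two-sided 0.05, with a standardized fall of 0.60 × (1 − k) and the same contrast SD throughout.

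| Scanned patients (assumed) | k = 0 | k = 0.25 | k = 0.5 | k = 0.75 | k = 1 |
|---|---|---|---|---|---|
| 20 | 0.72 | 0.48 | 0.25 | 0.10 | 0.05 |
| 28 | 0.86 | 0.63 | 0.33 | 0.12 | 0.05 |
| 40 | 0.96 | 0.79 | 0.46 | 0.15 | 0.05 |

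Under the same assumptions, the number of scanned patients needed to hold power grows by about 1/(1 − k)², which is 4 at k = 0.5. This models the mean change only, uncorrected. The planned group analysis also enters outcome and arousal change as regressors and tests correlations with them.

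**Step 4: the exclusion wording.** The sentence allows two readings.

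- *Literal:* negative words and non-words are out. The contrast then loses its comparator and its baseline. Nothing is subtracted, but the named contrast cannot be computed.
- *A slip, with negative written for neutral:* the contrast stands, the neutral words are expressly set aside as control variables, and Steps 1 to 3 apply. The non-words remain both excluded and the baseline.

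Under neither reading does the named analysis test the prediction in Objectives {7}.

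**The case against.** **Subtracting negative words is a legitimate control.** The construct is emotion processing related to self-criticism, and the background argues for individualized over standardized material. A comparison with neutral words would count general calming towards negative content as change in self-criticism processing. This stands, and it is why the existing contrast should stay. It does not make that contrast a test of an unqualified fall.

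**Cancellation is not demonstrated.** A reader might infer from the pilot that the contrast is bound to come out null. The pilot has five people, gives no estimate or equivalence margin, and reports no change over therapy for negative words. Only shared change cancels. The cited treatment studies help little. The insula decrease came from six inpatients in DBT on a reappraisal task. The finding that "decreased amygdalar reactivity was identified after DBT" concerns a region outside the predicted network. The trial's own feasibility pilot (N = 8) saw a trend to lower putamen activity on exposure to self-critical words, but its contrast is not stated. The objection therefore stands as to size: k is unknown.

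**The harm may stop at this one test.** A reader might infer that a null would carry into the mediation analysis. It could, but only if this contrast feeds the composite, and the plan does not say so.

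**The choice of regions is the investigators' own.** The study with individualized self-critical words found "bilateral insula activation, along with activations in left hippocampus and amygdalar formations", and a reader might infer that the network is wrongly specified without the amygdala and hippocampus. Naming fewer regions than one cited source found is an a priori choice and not an error.

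**Conclusion.** The point holds as a mismatch between hypothesis and test. Objectives {7} predicts a fall in activation. The one emotion-processing contrast named in Statistical methods {20a} estimates how much more self-critical words change than other negative words, and it keeps only a fraction 1 − k of any fall. This follows from algebra and needs no assumption beyond reading the contrast as first named in its sentence.

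The loss could be nil (k = 0) or complete (k = 1), and the documents do not locate k. The power figures show the sensitivity under assumed values and are not an estimate for this trial. They also assume an equal contrast SD, and the full recovery by the neutral-word contrast assumes a stable response to neutral words. The contradiction over excluded word sets is a firm defect on any reading. The main clinical outcome, the ZAN-BPD, is not affected.

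**What to change.** In the fMRI paragraph of Statistical methods {20a}, before the scans are analysed:

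1. Reconcile the sentence on word types, so that the conditions in the contrast and the baseline are not also listed as excluded, and give each stimulus set a stated role.
2. Pre-specify self-critical versus neutral words by time as the test of the prediction in Objectives {7}.
3. Keep self-critical versus standard negative words by time, labelled as the test of specificity to self-criticism.
4. State in advance the order of the two tests or how multiplicity is handled.
5. State which contrast supplies the regional change in the emotion-processing composite.

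The cost is one further contrast on scans already planned. The added contrast is less specific to self-criticism, so the two results should be reported and read together.
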